#### Sample size estimation

2.1.3

In a previous study of patients with peripheral neuropathy who received vitamin D supplementation for a 1.19-point reduction in MNSI physical examination score with a standard deviation of 1.29 points (46). We assumed a two-sided α error probability of 0.01 and a power of 0.95. We used PASS version 11 (NCSS, LLC. Kaysville, Utah, USA) to estimate the sample size. After estimation, the total sample size was 84 cases, with 42 in each group. Considering that 20% of the participants could be lost to follow-up or refusal of follow-up, we plan to enroll 53 patients per group (total 106 patients).

**Figure 2 f2:**
[figure not shown]
Schematic of five neurological examinations used to diagnose distal symmetric polyneuropathy **(A)** Ankle reflexes: The examiner should gently tap the Achilles tendon on one side of the subject’s foot using a percussion hammer. The ankle reflex is considered absent if the foot cannot be plantarflexed, weakened if the plantar flexion is not significant, and positive if the bilateral ankle reflexes are weakened or absent. **(B)** Vibration sensing: After striking a 128 Hz tuning fork, it is placed on the dorsal side of the big toe of both feet to observe whether the participants can feel the tuning fork’s vibration. Vibrational sensation is positive if the sense of vibration on either side disappears or decreases. **(C)** Temperature sensing: One end of the temperature tester (metal or polyester) is s placed on the skin of the dorsum of the foot (avoiding calluses, ulcers, scars, and necrotic tissue). The result is positive if the participant cannot correctly distinguish the temperature at either end. **(D)** Pressure sensing: A 10 g Semmes–Weinstein monofilament is placed on the dorsal side of the hallux with gradually increasing pressure, repeated four times on each side, eight times in total on both feet, and 1 point is recorded if no pressure is sensed once. The result is considered positive if the total score is ≥ 5 points. **(E)** Pinprick pain sensing: Gently prick the skin of the dorsum of the foot with the tip of a pin without causing skin damage. Participants who cannot feel pain or are hyperresponsive to pain are considered positive.

### Randomization, allocation concealment and blinding

2.2

All eligible participants will be assigned a unique identification number in the order of enrollment. Randomized assignment of subjects is fundamental to clinical trial design. While performing a simple sequence of random numbers can ensure independence among subjects and avoid potential selection biases, doing so has the potential to lead to an imbalance in the distribution of important covariates across treatment groups. Therefore, we will opt for the block randomization scheme (47). A person independent of the research center will generate a block randomization coding scheme using R software (version 4.1.2, R Foundation for Statistical Computing, Vienna, Austria). Next, all participants will be assigned in a 1:1 ratio to the placebo control or HDVD supplementation groups.

In order to avoid selection bias to the maximum extent possible, we will adopt the method of avoiding leakage of grouping information. The goal is to balance out all known and unknown factors between the two groups, so that differences in outcomes between the groups could ultimately be attributed to the effect of HDVD supplementation. To this end, we are going to use the method of allocation concealment. A staff member who determines the grouping of random sequences will not be involved in the inclusion of subjects. Neither our investigators nor our subjects are aware of the random sequence and the corresponding group during the diagnosis of DSPN, during the eligibility evaluation stage such as reviewing whether patients met the inclusion and exclusion criteria, and during the stage of soliciting patients’ willingness to participate in the trial.

Each protocol will be placed in an opaque envelope, marked with the code, and sealed. In order to reduce information bias, including measurement bias and implementation bias, we will double-blind the trial for the investigator and participants. Once the participants are enrolled, a third person, independent of the participant and investigator, will open the envelopes individually, and the executor will perform the corresponding injection per the envelope protocol.

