### Study design

2.1

We will conduct a multicenter, prospective, randomized, double-blinded, and placebo-controlled clinical trial. First, participants will be assigned to the HDVD supplementation or placebo control group in a 1:1 block randomization scheme. Next, intramuscular injections will be administered at baseline and 1 and 2 months later. Moreover, we will collect anthropometric measurement data, fasting blood glucose, β-cell function, hemoglobin A1c, and other biochemical data. Lastly, MNSI will be performed at baseline and 3 months later. This study will follow the Comprehensive Reporting Test Standard Guidelines (45). The study flow chart is shown in **Figure 1**.

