#### Study setting

2.1.1

We will recruit participants from four large hospitals: Longyan First Affiliated Hospital of Fujian Medical University, Longyan Traditional Chinese Medicine Affiliated Hospital of Fujian University of Traditional Chinese Medicine, Longyan Boai Hospital, and Longyan Shanghang County Hospital. All participants will provide written informed consent to participate in the study.

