### Data analysis

2.6

Any participant who completes the randomization will be included in the intention-to-treat set for data analysis. In cases when random or unforeseeable missing data occur, the missing data will be processed by multiple imputation method and sensitivity analysis will be carried out (49). The safety set which contains at least one safety assessment and adverse event report will be used to analyze the safety of HDVD supplementation. Quantile-quantile plot will be used to determine if the data conforms to a normal distribution. For descriptive analysis, the results of continuous variables (age and body mass index, among others) that conform to normal distribution will be expressed as mean ± standard deviation, and those that do not conform to normal distribution will be expressed as median and interquartile range. Categorical variables (sex and smoking status) will be expressed as frequencies and percentages.

Baseline data will be compared between the HDVD supplementation and placebo control groups. In HDVD supplementation or placebo control group, a paired sample t-test will be used for post-intervention versus pre-intervention comparisons. The difference value of MNSI before and after intervention will be performed by independent sample t-test test to compare the difference between the two groups. If the data does not conform to normal distribution, the Mann-Whitney U test will be used for analysis. The chi-square test will be used for categorical variables.

Furthermore, we will use the MNSI score before intervention as a covariate, and the F value will be calculated using analysis of covariance (ANCOVA) to analyze the change in the MNSI score after HDVD supplementation. Finally, if the number of adverse events occurring during the study is sufficient, the chi-square test or Fisher’s exact probability method will be used to compare differences in adverse events between both groups.

All data will be analyzed using the R software (version 4.1.2; R Foundation for Statistical Computing, Vienna, Austria). Additionally, all statistical analyses will be performed using a two-sided test, considering P < 0.05 statistically significant.

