The strength of this study design is that it will determine whether an improvement in neuropathy accompanies an increase in vitamin D concentration due to HDVD supplementation. Notably, DSPN is associated with muscle atrophy; thus, decreasing the quality of life. Although previous studies suggested that vitamin D supplementation may improve muscle strength (52, 54, 66), our study will explore the effects of HDVD from multiple dimensions, such as quality of life and muscle strength. We will use the Short Form-12 (SF-12) questionnaire, comprising eight domains, to assess the quality of life. The SF-12 has satisfactory validity and reliability, showing good internal consistency in the psychological (Cronbach’s α=0.83) and physical component summaries (Cronbach’s α=0.81) (67). Moreover, we will measure the maximum grip strength of both hands before and 3 months post-intervention to assess changes in muscle strength.

This study design has some limitations. First, the trial will be conducted only in China’s population with T2DM and DSPN. Therefore, the results may not be directly applicable to other ethnic groups. Second, the latitudes of southern China will be selected for this study; therefore, the results may not be directly applicable to other latitudes. Nevertheless, the study can provide certain evidence that may require further verification in other regional or international multicenter studies. Third, owing to the difficulty in recruiting patients with DSPN, it will be difficult to maintain a balance between the groups. However, we will further correct factors, such as age, sex, and body mass index, through stratified analysis and by applying the analysis of covariance statistical strategy as far as possible.

In conclusion, this study will provide clinical evidence demonstrating the efficacy and safety of post-treatment HDVD supplementation for DSPN. Additionally, if HDVD supplementation can improve neuropathy, this study will provide new directions for future pharmacological research and clinical management of diabetic neuropathy.

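### Block randomisation is justified as a remedy for covariate imbalance, which blocks without strata do not give; hospital is named in neither the allocation nor the ANCOVA, at a modest cost in precision

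*Protocol article*

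**What the plan says.** Section 2.2 (Randomization, allocation concealment and blinding) says of a simple random sequence that "doing so has the potential to lead to an imbalance in the distribution of important covariates across treatment groups", and goes straight on: "Therefore, we will opt for the block randomization scheme". Section 2.1 describes a "1:1 block randomization scheme". Neither section names a stratification factor or a block size. On numbering, section 2.2 says: "All eligible participants will be assigned a unique identification number in the order of enrollment".

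Section 2.1.1 makes the trial multicentre: "We will recruit participants from four large hospitals".

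For the covariance analysis, section 2.6 says "we will use the MNSI score before intervention as a covariate" and names no other covariate. The Discussion (section 3) lists as a limitation that "it will be difficult to maintain a balance between the groups", and plans further correction, so far as it proves feasible, by stratified analysis and ANCOVA. Its examples are age, sex and body mass index, in an open list. Hospital is not among them.

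**The concern.** The reason given for the design does not match what the design does. Blocking forces equal numbers in the two arms at the end of each block. It therefore balances arm totals and, approximately, calendar time. It has no mechanism for balancing age, neuropathy severity or hospital unless a separate block sequence runs within each level of that factor.

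Hospital is the natural stratum here. The Introduction explains that part of the MNSI is an examination performed by a physician, so examiners and case mix may differ between hospitals. If hospital is in neither the allocation nor the model, any hospital differences in MNSI change stay in the error term and widen the confidence interval of the primary comparison. Because the Discussion already expects imbalance and leaves its list of correction factors open, it is better to settle the treatment of hospital before unblinding.

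**Working it through.** **1. The plan's own sample size.** Inputs from section 2.1.3: difference 1.19, SD 1.29, two-sided alpha 0.01, power 0.95, 20% loss.

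n per arm = 2 × (2.576 + 1.645)² × (1.29/1.19)² = 41.87, so 42 per arm and 84 in total. With loss, 42/0.8 = 52.5, so 53 per arm and 106 in total. Both figures reproduce.

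**2. Do blocks balance a covariate?** Simulation of 106 patients, 20,000 runs, four hospitals equally likely for each patient, and a binary covariate with 50% prevalence. Block sizes of 2, 4, 6 and 8 are assumed, since none is stated.

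| Allocation | Mean difference in arm totals | Chance of a covariate gap of 15 points or more | Mean of the largest within-hospital arm difference (95th percentile) |
|---|---|---|---|
| Simple | 8.2 | 0.13 | 7.6 (13) |
| Blocks, sizes 2 to 8 | 0 to 0.9 | 0.14 | 6.1 to 6.2 (11) |

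Blocks fix the arm totals, leave the covariate no better balanced, and improve hospital balance only a little. In a separate 84-patient simulation, blocks formed within hospital cut the largest within-hospital difference from about 5.5 patients to about 1.2.

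**3. How unevenly could a hospital split?** This depends on hospital sizes, block size and recruitment order, none of which is stated. The table assumes 106 patients, one list and blocks of 4.

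| Hospital sizes | Recruitment order | Any hospital 60:40 or worse | Any hospital 65:35 or worse |
|---|---|---|---|
| 40/30/20/16 | fully interleaved | 76% | 38% |
| 27/27/26/26 | fully interleaved | 57% | 30% |
| 40/30/20/16 | one after another | 10% | 0% |
| 27/27/26/26 | one after another | 0% | 0% |

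**4. Cost of leaving hospital out of the model.** Let ρ be the share of variance in MNSI change that lies between hospitals (assumed). The standard error rises by the factor 1/√(1−ρ):

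- ρ = 0: 1.000
- ρ = 0.05: 1/√0.95 = 1.026
- ρ = 0.10: 1/√0.90 = 1.054
- ρ = 0.20: 1/√0.80 = 1.118

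The simulation (84 evaluable, four equally likely hospitals, total SD 1.29) compared one block list without hospital in the model against blocks within hospital plus hospital in the model. It gives somewhat smaller ratios of the average model standard error:

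- ρ = 0.05: 0.279/0.274 = 1.02
- ρ = 0.10: 0.277/0.266 = 1.04
- ρ = 0.20: 0.273/0.251 = 1.09

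Taking both together, the increase is roughly 2% to 12%. The formula does not involve how hospitals split between arms, so this figure measures omission from the model. It does not measure the imbalance in step 3.

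**5. Power at alpha 0.01, 42 per arm.**

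| ρ | One list, hospital ignored (total SD 1.29) | Blocks within hospital, hospital in model (total SD 1.29) | Hospital ignored, if 1.29 is a within-hospital SD |
|---|---|---|---|
| 0.05 | 0.949 | 0.953 | 0.939 |
| 0.10 | 0.949 | 0.962 | 0.924 |
| 0.20 | 0.953 | 0.980 | 0.886 |

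The first two columns are simulated, so differences well under a point carry no weight. The last uses the normal approximation with SD 1.29/√(1−ρ) = 1.32, 1.36 and 1.44, against 0.951 with no hospital effect. In every simulated setting the estimate was centred close to 1.19 and type I error stayed near 0.01.

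**The case against.** Several points on the other side stand.

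- **Unstratified is an inference.** The article names no strata, but neither does it say that one list spans all hospitals. Block size and strata are details that a condensed article may leave to the full protocol, which is not shown. A reader might conclude that the allocation is certainly unstratified; the text does not establish that. The faulty rationale in section 2.2 is stated outright and stands either way.
- **Further adjustment is planned.** The Discussion names age, sex and body mass index in advance, in an open list that could admit hospital. It would be unfair to say that adjustment is left wholly until after the data are seen. Hospital is nonetheless not named.
- **Blocks do balance something besides arm size.** They balance enrolment period and hence season, which is useful in a vitamin D trial.
- **The hospital effect may be small.** The outcome is change from baseline, so a stable difference between examiners largely cancels within patient, and all participants live in one city. No source in the article supports any particular value of ρ.
- **The split percentages are fragile.** The 76% figure needs full interleaving and unequal hospitals, and much of it comes from the two small hospitals. With sequential recruitment it falls to 10%.
- **Lists by hospital have a price.** The person giving the injection follows the envelope and may learn allocations, so a local block sequence makes the next allocation somewhat easier to guess.

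These points limit the size of the concern. They do not rescue the inference from covariate imbalance to blocking.

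**Conclusion.** The concern holds, as a faulty rationale with a modest cost in precision. Blocks without strata do not deliver the covariate balance for which section 2.2 chooses them, and hospital appears in neither the stated allocation nor the stated model.

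Omitting hospital raises the standard error by roughly 2% to 12% if 5% to 20% of the variance lies between hospitals, and by nothing if there is no hospital effect. That range is assumed.

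Two stronger readings are not supported. One is that the treatment comparison is biased: randomisation protects it, and the simulations show an estimate on target and type I error near nominal. The other is that the trial is underpowered: if 1.29 is the total SD, power stays at about 0.95 as planned, and what is forgone is a gain of up to about three points. A real loss, down to 0.886 at ρ = 0.20, arises only if 1.29 is a within-hospital SD, which section 2.1.3 does not say.

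Severity is minor to moderate.

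**What to change.** 1. In section 2.2, replace the rationale: blocking keeps arm sizes and enrolment period balanced, and balance on a covariate requires stratification. If the full protocol already stratifies by hospital, say so here.
2. If it does not, and enrolment still allows, generate a separate 1:1 permuted-block list for each hospital, with its own sealed envelopes and varying block sizes to limit prediction of the next allocation.
3. Before unblinding, prespecify hospital as a fixed effect beside baseline MNSI in the primary ANCOVA of MNSI change. This remains possible even if randomisation has started.

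The cost is four short lists in place of one, three degrees of freedom in the model, a few incomplete blocks that may leave the arms a patient or two apart, and slightly easier local prediction of allocation, which varying block sizes reduce.

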### Intervention

2.3

All participants will receive diabetes health education and follow-up. Medical nutrition therapy will be recommended for every patient with diabetes, and they will be advised to avoid overeating and undereating, which causes oxidative stress due to glucose fluctuations, exacerbating peripheral nerve damage. Moreover, self-monitoring of blood glucose will be recommended for every participant. The optimal blood glucose control target will be 4.4 mmol/L < fasting blood glucose < 7.0 mmol/L, 2-h postprandial blood glucose < 10.0 mmol/L, and avoid hypoglycemia. Next, exercise therapy, avoidance of foot injuries, and wearing white socks frequently will be recommended for every patient with diabetes to detect minor local injuries early.

After randomization, all participants will receive an intramuscular injection of the trial drug (vitamin D_2_ 600,000 units, 3 mL, monthly for 3 months) or placebo (0.09% sodium chloride 0.0027 g, 3 mL, monthly for 3 months) into the gluteus maximus. Vitamin D_2_ is produced by Jiangxi Gannan Haixin Pharmaceutical Co. Ltd. (Ganzhou, Jiangxi, China), and sodium chloride by Hubei Xinghua Pharmaceutical Co. Ltd. (Wuhan, Hubei, China). Each injection will be packaged in an opaque sealed package with an instruction leaflet and label. Drug dispensing will be performed by a third person independent of the implementer and participant. It is critical that all participants remain in the follow-up cohort as long as possible, and the efforts of all investigators and related personnel will improve participant adherence to the intervention and follow-up schedule. If the participant refuses to continue the follow-up, the investigator will determine the reason and encourage the participant to continue the intervention and follow-up.

### Outcome assessment

2.4

#### Primary and secondary outcomes

2.4.1

The primary outcome measure is the change in the mean MNSI score at baseline and 3 months post-intervention, reflecting the peripheral neuropathy status of the participant.

The secondary outcome measures include 1. changes in vitamin D level, including 25(OH) D_2_, 25(OH)D_3_, and 25(OH)D; 2. changes in fasting blood glucose, 2-h postprandial blood glucose, and hemoglobin A1c; 3. changes in fasting C-peptide and 2-h postprandial C-peptide; 4. changes in homeostasis model 2 for assessing insulin resistance, insulin sensitivity, and β-cell function (HOMA2-IR, HOMA2-%S, and HOMA2-%B, respectively) by HOMA2 software (version 2.2) available from the Oxford Centre for Diabetes, Endocrinology, and Metabolism (48).; 5. changes in systolic blood and diastolic blood pressure; 6. changes in triglyceride, total cholesterol, high-density lipoprotein cholesterol, and low-density lipoprotein cholesterol; and 7. changes in the maximum bimanual grip strength and quality of life score.

#### Demographic and anthropometric data

2.4.2

Baseline data will be collected at enrollment for all participants. The demographics will include name, age, sex, race, residence, occupation, marital status, and education. Anthropometric measurements will include height, weight, body mass index, waist circumference, and hip circumference. Additionally, we will measure vital signs, such as body temperature, heart rate, and blood pressure, simultaneously.

#### Clinical data collection and follow-up

2.4.3

Venous blood samples will be collected from participants at baseline and designated visit points for biochemical data, such as lipid, glucose, and uric acid. The method of venous blood sampling is as follows. First, the participants will fast for 10–12 h, and a qualified nurse will collect blood samples at 6:30–8:30 am. Next, the blood samples will be tested for 25(OH)D_2_, 25(OH)D_3_, and 25(OH)D levels using high-performance liquid chromatography-tandem mass spectrometry (LC-MS/MS) at the Fuzhou King Med Clinical Laboratory (Fuzhou, Fujian, China). The executive assistants involved in data collection and evaluation will be blinded to participants’ groupings. All clinical data collection processes are presented in **Table 2**.

**Table 2 T2:** Participant flow of enrolment, intervention, and outcome measurements.

		PS	M0	M1	M2	M3
Enrolment	Recruitment	√				
	Eligibility Screening	√				
	Signed written informed consent	√				
	Allocation		√			
Intervention	Health education, medical nutrition therapy, exercise therapy, self-monitoring of blood glucose, and disease follow-up		√	√	√	√
	High-dose vitamin D_2_ /placebo injection		√	√	√	
Outcomes	Demographic characteristics and basic information (sex, age, marital status, place of residence, and education level)		√			
	Personal life status (smoking status, drinking status, beverage intake status, sunshine reception, living alone, and menstrual status for females)		√			
	Duration of diabetes, strict diet control, and moderate aerobic exercise for >150 min per week		√			
	Number of self-monitoring of blood glucose per week and occurrence of hypoglycemia		√			
	Comorbidities (hypertension, hyperuricemia, obesity, osteoporosis, and nonalcoholic fatty liver disease)		√			
	Other diabetic complications (diabetic retinopathy, diabetic nephropathy, diabetic foot ulcer, coronary atherosclerotic heart disease, cerebrovascular disease, and peripheral vascular disease)		√			
	Anthropometric measurements (height, weight, body mass index, waist, and hip circumference) and blood pressure (systolic and diastolic blood pressure)		√			√
	Metabolic parameters (FBG, 2hBG, HbA1C, FCP, 2hCP, triglycerides, total cholesterol, HDL-C, LDL-C, uric acid, HOMA2-IR/%S/%B)		√			√
	Intima-media thickness of carotid and dorsalis pedis artery by ultrasound, fundus examination, bone mineral density		√			√
	25-(OH) Vitamin D_2_, 25-(OH) Vitamin D_3_, and 25-(OH) Vitamin D tested by LC-MS/MS method		√			√
	Maximum bimanual grip strength measured by a dynamometer		√			√
	Short Form -12 Quality of Life Questionnaire		√			√
	MNSI score		√			√

PS, prior to study; M0, baseline assessment; M1, 1 month from baseline; M2, 2 months from baseline; M3, 3 months from baseline; HOMA2-IR/%S/%B; homeostasis model assessment index 2 for assessing insulin resistance/insulin sensitivity/function of islet β-cells; LC-MS/MS, liquid chromatography-tandem mass spectrometry; ^*^MNSI, Michigan Neuropathy Screening Instrument; FBG, fasting blood glucose; HbA1c, hemoglobin A1c; 2hBG, 2-h postprandial blood glucose; FCP, fasting C-peptide; 2hCP, 2-h postprandial C-peptide; HDL-C, high-density lipoprotein cholesterol; LDL-C, low-density lipoprotein cholesterol.

